# “The educating nursing staff effectively (TENSE) study”: design of a cluster randomized controlled trial

**DOI:** 10.1186/s12912-014-0046-6

**Published:** 2014-12-19

**Keywords:** Dementia, Challenging behaviour, Training, Nursing staff, Stress, Work satisfaction

## Abstract

**Background:**

Challenging behavior exhibited by people with dementia can have adverse outcomes, like stress, low morale, low work satisfaction and absenteeism for nursing staff in long-term care settings. Training nursing staff to manage challenging behavior may reduce its impact. Although much of the research into training nursing staff shows methodological limitations, several studies find some effect of training programs on knowledge about and on management of challenging behavior. Effects on stress or burnout are almost not found.

**Methods/Design:**

The TENSE-study is a randomized controlled study on 18 nursing home units (9 control, 9 intervention) investigating the effects of a continuous educational program for nursing staff about managing challenging behavior. Nursing staff of intervention units receive the program, nursing staff of control units do not and continue usual care. The primary outcome is stress experienced by nursing staff (N = 135). Secondary outcomes are: emotional workload, work satisfaction, stress reactions at work and knowledge about challenging behaviour of nursing staff; and frequency of challenging behavior, quality of life and social engagement of residents (N = 135). Because there are many unknown factors influencing the effect of the training, a process evaluation to evaluate sampling-, implementation- and intervention quality as well as barriers and facilitators to implementation will also be included in the analysis. Nursing staff could not be blinded to the intervention, but were blinded for the outcomes.

**Discussion:**

Strengths of this study are the (good) description of the intervention complemented by a process evaluation and the tailoring of the intervention to the wishes and needs of the nursing homes at any moment during the study. Sustaining the effects of the intervention by using follow up sessions is another strength. Possible drawbacks may be dropout because of the frailty of the elderly population and because nursing staff might move to another job during the study.

**Trial registration:**

NTR (Dutch Trial Registration) number NTR3620

## Background

Working with residents with dementia is enervating for nursing staff. Up to 97% of nursing home residents with dementia exhibit challenging behavior during the course of the dementia [1]. Challenging behavior is associated with adverse outcomes in nursing staff, such as anxiety, less work satisfaction, emotional exhaustion [2,3], physical health stress and burnout [4]. Agitated behavior, and physically aggressive behavior in particular, is strongly related to distress in nursing staff, especially if this behavior is perceived as threatening [4-6]. In addition, if the cause of the behavior is unclear [7] or if nursing staff anticipates aggressive behavior [7,8] and consider themselves not adequately equipped to manage the behavior, they are prone to experiencing stress [9,10]. Stress can lead to low morale, absenteeism from work and high staff turnover [4]. It can also negatively affect the interaction with residents and thus the quality of provided care [11]. Decreasing adverse outcomes of challenging behavior for nursing staff may be accomplished by training them to better manage the behavior [12].

Many studies into educational programs for nursing staff in long term care settings have very small sample sizes, non random designs, designs without control groups or a low response rate [13,14]. Only a minority of these programs is evaluated in an RCT-design.

Studies of the effect of educational programs for nurses regarding challenging behavior generally focus on knowledge [15-24]; management skills to decrease or cope with challenging behavior[19,24-31]; stress experienced by nurses [16,17,19,24,26,29,32,33] and/or resident behavior [2,19,21,24-26,28,34-36].

Although most studies that focused on knowledge found an increase in knowledge [15,17-24,37], there is minimal evidence that the increased rates of knowledge can be sustained [13]. Only one of the three available RCT’s [17,19,21] reports on follow up meetings and found an increase in knowledge post intervention at three and six months follow up [19]. Follow up sessions to update knowledge are highly recommended by several authors [14,22,25,29,31,32,38].

Studies that focused on management skills resulted in (significant) improvements in different nursing skills. [18,24-29,31]. Three of these studies, two RCT’s [25,26] and one using a quasi-experimental pre- and posttest design [31], succeeded in sustaining these improvements.

Of the studies that focused on stress, one RCT [32] and two quasi experimental pre- and post design studies [16,29], found a small effect: The RCT [32] found an increase in stress in the control group but not in the intervention group which was given a training followed by making individual care plans and supervision of a psychiatric nurse. One quasi experimental study [16] found that nursing staff viewed the task of care giving as less frustrating and more rewarding, the other [29] found that after the intervention nursing staff showed fewer stress. Two RCT’s [17,19] found no effect.

Of the studies that focused on challenging behavior the non-RCT studies [2,19,26-28,36] found no differences in challenging behavior of the residents. Three RCT’s [21,34,35] and a controlled study [25], found an effect of training programs for nurses regarding challenging behavior on the behavior of the residents. Two of those [34,35] found a significant decrease in the total agitation scores as measured by the CMAI, and two [21,34] found significant decreases on physically non-aggressive behavior and on verbally aggressive behavior. Only one study [21] found a significant effect on aggressive behavior, which was also measured by the CMAI.

In summary, studies show effects on knowledge. However, there is little evidence for sustaining these effects in the long term. In general, studies that focused on management skills found an effect. A sustained effect was found on management skills and resident behavior outcomes for some of the training programs that use a kind of follow up. There are three studies that found lasting effects on outcomes for nursing staff as well as outcomes for residents [21,25,34].

Almost no effects on stress were found. In general, there are only a few high quality studies that investigated the long term effect of the interventions [19,25,26,29,31,32]. Thus, more than a decade after the conclusion of Aylward et al. [14] that there is a lack of rigorous research into the effectiveness of continuous education programs in long term care, this lack still exists.

Besides the quality of the studies, there is also a problem with the description of the educational programs. These were often poorly or not described so we are unable to judge the quality of these programs. Some of the studied programs did not combine knowledge with skills training [11,15,16]. Furthermore, because of the lack of description of the follow up sessions, it is not possible to evaluate whether the programs were tailored enough. An educational program has to support various learning styles of the participants [39-41]. Studies about learning styles of nurses found that (student) nurses have a mix of all learning styles [39,40], but that more than half have a predominantly concrete learning style and almost half a reflective learning style [42]. This implies that training generally has to be interactive and multifaceted [39-41].

An important factor needed for sustaining the results is integrating the educational program in daily practice by tailoring it to individual needs and the needs and interest of the care-organization [37]. We hypothesize that implementation of an educational program that does not have the aforementioned shortcomings will more likely result in a decrease of distress experienced by the nursing staff and a decrease in frequency of challenging behavior. Therefore, we developed an educational program for nursing staff on challenging behavior that is tailored to the wishes and needs of the care-organization and combines various learning styles.

The aim of our study is to determine, in a randomized design that accounts for clustering within units, the effect of a new educational program in the short and in the mid- term on stress experienced by nursing staff (primary outcome), emotional workload, work satisfaction, stress reactions at work and knowledge about the origin and the management of challenging behavior of nursing staff and challenging behavior of the residents. We will also determine the effect of the program on Quality of Life (QoL) and social engagement of residents as stress and work satisfaction may influence the way residents are treated by nursing staff. Possibly intervening factors such as attitude about people with dementia, the organizational culture, the time residents have lived on the unit and the time nursing staff works on the unit are measured as well.

## Methods

### Design

The TENSE-study is a cluster-randomized, controlled study on dementia special care units (DSCU) of Dutch nursing homes from different regions of the Netherlands. Nursing homes will participate after consent of the management, the unit managers, nursing staff, the board of representatives of residents and the psychologist. Eighteen units (clusters) will be randomized with a block size of 2. From each of 9 nursing home organizations, two units are included, one of which becomes an intervention unit (receives a training program) and one becomes a control unit (no training, continuing usual care). This results in nine intervention units and nine control units. Allocation to intervention or control was determined through the tossing of a coin by an independent researcher unfamiliar with the study and blinded for the nursing homes. To prevent contamination, the nursing homes need to agree that the control and the intervention unit do not have the same physician and psychologist and that nursing staff members are not employed at both units during the study period. Units are preferably at a different location.

The duration of the follow-up will be 9 months. A 3-day course (three times 2,5 hours) for intervention units will be held immediately after baseline (T0), with follow up sessions after three and six months. Assessments will take place at baseline (T0), immediately after the course (T1), just before follow up session 1 (T2), and nine months after the 3 day course (T3). Table 1 gives an overview of the measurements (see Figure 1).

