**Design of the TENSE-study.**

### Inclusion criteria

Nursing homes will be included if:they have at least two DSC Units;nursing staff members, psychologist and physician work on one of these units exclusively;one care team cares for at least fifteen residents that are diagnosed with dementia;participating units have not planned a reorganization or other interventions that can influence the study within half a year before or during the study.

Inclusion criteria for residents are:dementia according to DSM-IV-TR criteria [43],living in the nursing home for more than one month.

Inclusion criteria for the nursing staff are:being employed for at least three months and not expected to be transferred to another unit within the study period,working more than one day a week.

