### The intervention

The educational program has three core elements for increasing its usefulness:an individually tailored make up based on interviewing staff, management and nursing staff about their wishes and needs;two follow up sessions, to enable continuous education;supervision, monitoring, facilitation and stimulation by the psychologist, middle management and other staff on the use of the newly learned techniques.

It has the following content:providing knowledge about dementia,educating about the origins of challenging behavior and how to manage it,educating how to recognize distress caused by challenging behavior in yourself and in colleagues,practicing how to gather information on resident and environmental factors that cause challengingbehavior,practicing how to signal signs of impending challenging behavior,practicing general behavior management skills that can be used in approaching the resident,practicing how to use a standardized method to manage challenging behavior, which is integrated in the multidisciplinary work processes and forms that are used in the nursing home.

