### The process of implementation

Before the 3-day course starts an extensive semi structured interview is conducted by the trainer with the psychologist, the elderly care physician (ECP) [50], the team manager and some members of the nursing staff to explore current (multidisciplinary) work processes and collect wishes and needs of the institution for tailoring the program. In this interview the following topics are discussed (1) in what way does the actual way of working differ from an ideal situation? (2) the context for change; is the nursing staff motivated to change?, (3) in what way does the organization supply help to facilitate changes in work processes. (4) what barriers and facilitators for the process of change exist in the nursing home. After the interview a plan is presented to the care-organization which describes in what way the intervention is tailored to the care-organization by training the elements that need to be changed [51]. The researcher receives the forms used by nursing staff on the unit for observing and analyzing behavior and for making a behavioral management plan, and incorporates these forms into the educational program. This way, nursing staff will not be confronted with new forms which differ from the ones they use in daily practice. The training program was provided by a very experienced professional trainer of nursing staff.

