#### The course

The 3-day course is offered to the complete unit-team and consists of three lessons of 2.5 hours, provided once per week or, once every two weeks. During the course, several team members are made responsible for various tasks, such as observing the resident’s behavior; observing stress caused by the challenging behavior; making an action plan; controlling the use of the plan; and involving the physician and/or psychologist at the right moment. Furthermore, the unit managers also receive the training so they can facilitate and reward the use of the newly learned techniques. Two follow up sessions are carried out. These are designed to stimulate the process of managing challenging behavior methodologically and are tailored to the situation in the organization.

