#### Third session: a plan of action

Before the third session nursing staff gathers the information they need and also read a paper about making a plan of action [52]. The third session concerns making the action plan. Nursing staff learn to use the sequence of “problem – goal – action” to decide what action has to be taken. Nursing staff decides which aspects of the training they want to practice in the next three months.

Subsequently, the trainer writes a report about the training that consists of the way participants want to manage the challenging behavior after the training and the wishes for future training and sends it to the psychologist of the nursing home. The psychologist, the unit manager and the elderly care physician can use it to support the nursing staff in managing challenging behavior and incorporate what they have learned in daily practice.

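### The anti-contamination rule for paired units leaves out the unit manager, who is trained and supports the programme, so a pair under one manager is eligible

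*Protocol article*

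**What the plan says.** All places are in the Protocol article, Methods.

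- **Pairing (Design).** "From each of 9 nursing home organizations, two units are included", one per arm.
- **Separation rule (Design).** With the stated purpose of preventing contamination, homes must accept this condition: "the control and the intervention unit do not have the same physician and psychologist and that nursing staff members are not employed at both units". On distance the text adds only: "Units are preferably at a different location".
- **Separation rule (Inclusion criteria).** A home qualifies if "nursing staff members, psychologist and physician work on one of these units exclusively".
- **Core element (The intervention).** One of three is "supervision, monitoring, facilitation and stimulation by the psychologist, middle management and other staff on the use of the newly learned techniques".
- **Who is trained (The course).** Besides the unit team, "the unit managers also receive the training so they can facilitate and reward the use of the newly learned techniques".
- **After the course (Third session: a plan of action).** The trainer sends a report to the psychologist, and "The psychologist, the unit manager and the elderly care physician can use it to support the nursing staff in managing challenging behavior".
- **Tailoring.** The team manager is interviewed before the course (The process of implementation), and the unit manager before the follow-up sessions (Follow-up sessions).

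No section requires the two units of a pair to have different managers.

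**The concern.** With both arms inside the same organisation, the contrast depends on keeping the programme out of the control unit. The plan recognises this and sets a rule, but the list of roles does not match its own account of who supports the programme. Three functions support staff after the course: psychologist, physician and unit manager. The first two may not be shared within a pair. The third may be, and it is the only one of the three that the course section names as receiving the training.

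A site applying the rule literally could enrol two units under one manager. That manager would attend the course and be equipped to encourage the techniques, while also running a unit that is meant to continue usual care. Anything carried across would make the control unit more like the intervention unit and bias the primary comparison towards no effect. The Background already reports that effects on stress have hardly been found, so there is little room for avoidable dilution.

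**Working it through.** **Step 1: compare the roles with the rule.**

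| Role | Part in the programme | Sharing within a pair barred? |
|---|---|---|
| Nursing staff | Trained as a team | Yes (Design; Inclusion criteria) |
| Psychologist | Core-element support; receives and can use the report; interviewed for tailoring | Yes (both places) |
| Physician | Can use the report; interviewed before the course | Yes (both places) |
| Unit or team manager | Trained; core-element support as middle management; can use the report; interviewed before the course and the follow-up sessions | No (neither place) |

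The gap appears in both places where the rule is stated.

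**Step 2: inputs for an illustration of size.** The Sample size section gives a 4-point difference on Emotional Exhaustion, alpha 0.05, power 0.80, a correlation of 0.6, an ICC of 0.05, and 121 staff per group, raised to 135 (nine units of 15). Sidedness is not stated; two-sided is assumed. No standard deviation is given, so 121 cannot be reproduced independently. Solving backwards with variance factor (1 − 0.6²) × [1 + (m − 1) × 0.05] gives an SD of about 10.65 for m = 15, 10.21 for m = 18 and 9.94 for m = 20. The steps below need no SD; they take the stated power as given.

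**Step 3: dilution at the stated power.** The standardised signal at 0.80 power is 1.960 + 0.842 = 2.802. If control units receive a fraction f of the effect on average, the contrast is 4 × (1 − f) and power is Φ[(1 − f) × 2.802 − 1.960].

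- f = 0.10: contrast 3.6 points; 0.9 × 2.802 − 1.960 = 0.562; power about 0.71.

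**Step 4: the planned 135 per arm.** With unit size fixed, the signal grows by √(135/121) = 1.056, to 2.960.

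- No carry-over: 2.960 − 1.960 = 1.000; power about 0.84.
- f = 0.10: 0.9 × 2.960 − 1.960 = 0.704; power about 0.76.

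**Step 5: what an average f means.** If k of 9 pairs share a manager and each such control unit receives a fraction c of the effect, then f = c × k/9. Both k and c are assumptions. At 135 per arm:

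| k | c | Contrast (points) | Power |
|---|---|---|---|
| 0 | – | 4.00 | 0.84 |
| 1 | 0.25 | 3.89 | 0.82 |
| 3 | 0.25 | 3.67 | 0.77 |
| 3 | 0.50 | 3.33 | 0.69 |

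The loss is small if one pair shares a manager and material if several do with sizeable carry-over. The documents do not say which applies.

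**The case against.** The strongest reply is that the problem is hypothetical. No section reports a shared manager, and the wording ties the role to the unit: the unit managers consent, the unit managers are trained. This is also a condensed article, and the full protocol may name more roles. What stands is that the number of affected pairs is unknown and may be zero. What does not stand is that the omission is mere condensing: the article states the rule twice, with the same three roles each time, and unit-based wording does not require different managers.

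Second, the manager's part is permissive. Managers are trained so that they can encourage use of the techniques, and they can use the report; nothing obliges them to drive the programme. The techniques are taught to the intervention team on cases from its own unit, and control nurses do not get that. This stands and suggests that carry-over would be partial. It does not remove the mismatch, because the psychologist and physician have the same permissive role and are nevertheless kept separate.

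Third, separate locations would limit spill-over. True, but they are only preferred.

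Three stronger readings are tempting and are not supported:

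- **That the tailoring spreads the programme across the organisation.** A reader might infer this because "After the interview a plan is presented to the care-organization which describes in what way the intervention is tailored to the care-organization". But the same section takes forms the unit already uses into the course and describes no revised forms, and Follow-up sessions speaks of fitting the programme to the unit.
- **That a null result could not be told apart from spill-over.** Table 1 schedules the knowledge test at T0, T1 and T3, and nothing confines it to intervention units, so a rise in control units would be a signal. The closing interviews in the Process evaluation also ask about perceived changes on the unit.
- **That dilution would be greatest at T3.** Nothing in the article bears on its timing.

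**Conclusion.** The point holds as a gap in a stated rule. The separation rule omits a role that the plan trains and relies on for support, so following it to the letter admits pairs with a shared, trained manager. The direction of any resulting bias is towards no effect. Its size cannot be derived from the article: the 10% average carry-over behind the fall in power from 0.80 to about 0.71 (or from 0.84 to about 0.76 at 135 per arm) is assumed, as are the two-sided test and the planned power itself. A reader might infer that control units were in fact contaminated; the article does not show that. The correction is worth making because the omission runs against the plan's own reasoning and is cheap to close.

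**What to change.** In both Design and Inclusion criteria, add the unit or team manager to the roles that may not be shared between the two units of a pair.

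Allocation is reported in the past tense, so for pairs already allocated:

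- record in the process evaluation whether the two units share a manager;
- repeat the primary-outcome analysis without the pairs that do, as a sensitivity analysis.

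**Cost.** A few organisations may have to offer a different second unit. The sensitivity analysis loses precision: if three of nine pairs were dropped, 90 staff per arm would remain, the standard error would rise by √(9/6) = 1.22, and power for an undiluted 4 points would be Φ[2.802 × √(90/121) − 1.960] = Φ(0.457), about 0.68. It should therefore be read as a check on the direction and size of the estimate, not as a second test. Recording the manager adds one item per pair.
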